#### Neurological examination

PD symptoms and severity including non-motor symptoms will be measured using the Movement Disorders Society Unified Parkinson’s disease Rating Scale (MDS-UPDRS) [35]. The non-motor symptoms scale (NMSS) [36] and the Parkinson’s disease questionnaire-39 (PDQ-39- quality of life) [37] will be used to assess the full spectrum of PD symptoms. Hand-eye coordination and manual dexterity will be tested using the nine-hole peg test [38]. Mood and cognition will be assessed by the Montreal cognitive assessment (MoCA), the CLOX II test and the geriatric depression scale (GDS).

#### Gait and balance

Performance tests measuring different aspects of gait and balance will be performed. Walking velocity will be tested under single and dual-tasking conditions [39, 40]. The patients will be instructed to walk a distance of 4 m at self-preferred speed. The required number of steps will be reported as outcome. The Timed-Up-and-Go-test (TUG) measures the basic functional mobility [41]. Freezing of Gait (FOG) is assessed by letting the patient make a 360° turn with small steps (approximately 25% of their own preferred step length) and walking fast with short steps [42]. To test axial symptoms, tandem gait at a self-preferred speed is recorded for at least 10 consecutive steps without a visual guiding line [43]. The Single Leg Stance test (SLS) will be used to test static balance and postural instability [43–46]. Finally, postural stability will be recorded by the Pull-Test (item 3.12 MDS-UPDRS).

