The current multicentre observational, cross-sectional VIP study: “Visual Impairment in Parkinson’s disease” is designed to promote knowledge about and recognition of symptoms, signs and causes of disturbed vision in people with PD. Our specific goals are to: (1) validate a screening questionnaire that aims to identify PD patients who should be referred to an ophthalmologist for further assessment; (2) determine the prevalence and severity of visual problems in PD; (3) study the impact of ophthalmologic disorders on clinical functioning (in particular on gait and balance control); and (4) explore treatment options for ophthalmologic disorders in PD, as a basis for future guideline development.

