#### Procedures and assessments

All assessments will be performed during regular medication use, preferably in an “ON-state”. The assessment will start with obtaining demographics and medical history. The neurological and ophthalmological assessments consist of an extensive test battery (Table 3).

**Table 3 Tab3:** List of assessments

Outcome	Ophthalmological Assessment
	*Subjective ophthalmological assessment*
Visual acuity	ETDRS logMAR
Reading speed, near visual acuity	Radner Reading Chart
Visual fields	Humphrey field analyser 30–2, Amsler grid
Contrast vision	Low-contrast letter charts (Pelli-Robson),
Colour vision	Ishihara plates/Farnsworth Munsell hue test (desaturated 15D)
Ocular motility	Eye follow movements, Cover test 30 cm and 6 m, Prism test (15 diopter), Eye-Tracking
Facial emotion recognition	Emotion Recognition Inventory (ERI)
Visual function	VFQ-25, Visual impairment screening questionnaire
	*Objective ophthalmological assessment*
Lens opacity	Slit lamp examination
Fundus appearance	Color Fundusphotography (7-fields)
Corneal thickness	Pachymetry
Intraocular pressure	(Goldmann) tonometry
Tear production	Schirmer’s test, TearFilmBreakUpTime, eye blink rate
Anatomical changes of the retina including thickness	Spectral-domain OCT (Heidelberg)
Retinal micro vascular changes	Angio-OCT (Heidelberg)
Outcome	Neurological assessment
PD-related disability and impairment	MDS-UPDRS, Schwab & England activities of Daily living, NMSS, PDQ-39.
Gait and Balance	Timed Up and Go test, Single Leg Stance test, Gait Speed (4 m walking), Dual tasking, Freezing of Gait, Tandem gait
Hand-eye coordination	9 Hole Pegboard test
Cognitive function	MoCA, CLOX
Mood	GDS

List of study protocol assessments, divided in ophthalmological and neurological assessment

Abbreviations: *EDTRS* Early Treatment of Diabetic Retinopathy Study, *D* diopter, *OCT* optical coherence tomography, *NMSS* non-motor symptoms assessment scale, *PDQ-39* Parkinson’s Disease Questionnaire, MoCA [47], Montreal Cognitive Assessment, CLOX, clock drawing test [48], GDS, Geriatric depression scale [49], VFQ-25, visual functioquestionnaire [72, 73]

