
### Statistical analysis plan

95% Confidence intervals, means, standard deviations and frequency distributions will be calculated for all outcomes. Nonparametric variables (age, disease duration, LED, total score VIPD-Q) will be expressed as the median, interquartile range (IQR), minimum, and maximum. To compare groups, we will use the student’s t-test for parametric continuous variables and the Mann-Whitney U test for non-parametric continuous variables. All analyses will be performed with SPSS 22.0 (SPSS Inc., IBM, Chicago, IL, USA).

To address the first study objective (validity of the screening questionnaire), we will compare the results of the VIPD-Q with the ophthalmological assessments using analysis of intraclass correlation coefficient (ICC), with Cohen’s kappa. The results of the ophthalmological assessments will be categorized in visual disorders within the domains of the VIPD-Q (ocular surface, intra- ocular, oculomotor and optic nerve). We hypothesize moderate to good correlation (ICC > 0.5) between the scores on the domains based on the ophthalmological tests and the scores on the domains based on the screening questionnaire. We will also address correlation for the total score. In addition, we will calculate optimal cut-off points of the domains and total score of the VIPD-Q using the receiver operating characteristic (ROC).

For the second and third objective (determine the prevalence and severity of visual problems in PD; impact on clinical functioning), PD patients will be compared with healthy controls using chi-square-tests for categorical values (sex, education, co morbidity, visited ophthalmologist, visual aid, vision changes during the day, difficulties with daily activities, impact on quality of life) or Mann-Whitney U test for non-parametric continuous variables (age, total score VIPD-Q, score per domain). Furthermore, the relationship between falling, disease duration, MDS-UPDRS, hand-eye dexterity, gait and balance tests, and visual problems will be assessed using multiple linear regression analysis.

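### The 4 m walk is described as a test of walking velocity, but its stated outcome is a step count, which gives mean step length and not speed

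*Protocol article*

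**What the plan says.** In the protocol article, Table 3 (section on procedures and assessments) gives the gait and balance row as "Timed Up and Go test, Single Leg Stance test, Gait Speed (4 m walking), Dual tasking, Freezing of Gait, Tandem gait". The 4 m walk is therefore labelled there as a speed measure.

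The section on gait and balance opens the description of this test with "Walking velocity will be tested under single and dual-tasking conditions". It continues: "The patients will be instructed to walk a distance of 4 m at self-preferred speed". The next sentence gives the scoring rule: "The required number of steps will be reported as outcome". Neither this section nor Table 3 mentions timing the walk or a result in metres per second.

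The test serves the third objective, the impact of ophthalmologic disorders on clinical functioning, "in particular on gait and balance control" (Background). The statistical analysis plan section says that the relationship between, among others, "gait and balance tests, and visual problems will be assessed using multiple linear regression analysis". It does not say which variable from the 4 m walk is meant.

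**The concern.** The quantity announced and the quantity scored are different. Velocity is distance over time, whereas a count of steps over a fixed distance has no time in it. This is more than a missing detail: the article does name an outcome for the walk, and that outcome does not measure what the same paragraph and Table 3 say is being tested.

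The risk is mislabelling. If the step count is reported under the heading of gait speed, readers will take a finding about step length as a finding about walking velocity. A patient who slows by taking fewer steps per minute, with the same step length, would have an unchanged result. The same applies to the comparison of single-task and dual-task walking: two step counts do not show whether velocity changed between the conditions.

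**Working it through.** The plan gives no figure to reproduce here, and no sample size or power is involved. The check is one of dimensions, followed by an illustration.

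**Inputs from the protocol article**
- Distance: D = 4 m (section on gait and balance; Table 3).
- Pace: self-preferred (section on gait and balance).
- Stated outcome: number of steps, n (section on gait and balance).
- Walking time, t: not stated.

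**What the stated outcome yields**
- Mean step length = D/n = 4/n metres.
- Speed = D/t = 4/t metres per second.
- Equivalently, speed = (4/n) × cadence, where cadence = n/t. Cadence needs t.

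With D and n known and t unknown, step length is determined and speed is not. This holds for any number of steps.

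**Illustration (the step count and cadences are assumed; the documents give neither)**

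Take n = 8, so mean step length is 4/8 = 0.50 m.

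| Assumed cadence (steps/min) | Time = 8/cadence × 60 (s) | Speed = 4/time (m/s) |
|---|---|---|
| 80 | 6.0 | 0.67 |
| 100 | 4.8 | 0.83 |
| 120 | 4.0 | 1.00 |

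The same recorded outcome, 8 steps, fits speeds from 0.67 to 1.00 m/s. The ratio is 1.00/0.67 = 1.5, which is simply the ratio of the cadences, 120/80.

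**Comparison within the article**

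Two other rates are given scoring rules that contain time. Reading speed is scored in words per minute (subjective assessment), and blink rate is blinks per minute over a 3-minute interval (objective assessment). The walk is the rate measure whose stated score has no time in it.

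**The case against.** The strongest reply is that the article does not say that steps are the sole outcome. Testing velocity over a set 4 m implies a stopwatch, and the steps may be reported alongside the time. The article condenses a full protocol (version 3.0, not shown) that may specify the timing. The same pages give no scoring unit for the Timed Up and Go, the Single Leg Stance or the nine-hole peg test, and nobody would infer that those are untimed.

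Much of this stands. Absence of timing in the article does not prove that no times were taken. Table 3 lists gait speed as an assessment within the gait and balance row, so speed is not itself the entry in the outcome column.

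What does not stand is that this is ordinary condensation. For the other tests the article is silent about the score. For the walk it states one, and it is a count that does not match the construct.

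A reader might go further and infer that the study has no walking-speed data at all, that a planned dual-task cost measure is lost, or that the regression will use steps in place of speed. The documents support none of these. Times may exist under the full protocol, no dual-task cost is defined as an outcome, and the analysis section does not identify the walk variable. Nor does the size of one step set a threshold for detecting slowing: slowing through cadence alone leaves the count unchanged at any size, while slowing through shorter steps can alter it.

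**Conclusion.** The conflict is real and should be resolved: the description and Table 3 name velocity or gait speed, and the scoring rule names a count that determines step length. That conclusion rests on the definition of speed and on the article's wording, and needs no assumed values. The 1.5-fold range is only an illustration of how loosely a step count constrains speed, and depends on the assumed 8 steps and 80 to 120 steps per minute.

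Confidence is high that the wording is inconsistent. Whether time was actually recorded cannot be settled from the article.

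The weight is modest. This is one of several measures for the third objective. The Timed Up and Go, Single Leg Stance, tandem gait, freezing and Pull-Test assessments are unaffected, as are the questionnaire validation and the prevalence estimates.

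**What to change.** Reconcile Table 3 with the section on gait and balance, according to what data exist:

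- **Where walking time was or can be recorded:** name walking speed, 4 m divided by time in seconds, as the outcome for each condition (single and dual task). Keep the step count as a second outcome, which gives mean step length 4/n.
- **Where no time exists:** rename the measure step count or mean step length in both Table 3 and the text, and draw no conclusion about gait speed from it.

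In either case, report how many patients contribute a speed.

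The cost is one time field per condition for any patients still to be assessed. The limitation is the calendar. According to the trial status section, phase 2 recruitment began in May 2017 and was expected to be complete by May 2019; the article was published on 25 June 2019. Many or all patients may already have been tested. If their times are not on the source records, speed will be missing for them, and relabelling, which needs no new data, is the remedy left.

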### Ophthalmological assessment

#### Subjective assessment

Some of the ophthalmological assessments require responses from the patient and are therefore defined as subjective measurements. The outcomes are visual acuity, visual field testing, contrast sensitivity, colour vision, ocular motility, facial emotion recognition and the visual function questionnaire (VFQ-25) concerning visual function. We start the assessment with measuring the best corrected visual acuity at distance, by using the Early Treatment of Diabetic Retinopathy Study (ETDRS) chart at 6 m [47]. 20/30–20/60 is considered mild vision loss, or near-normal vision, 20/70–20/160, moderate visual impairment and 20/200–20/400 severe visual impairment. This is followed by testing reading or near visual acuity, tested with the Radner reading charts at 40 cm distance [48]. Reading correction is applied if applicable. The reading speed is scored in words per minute. Possible visual fields deficits including problems in the peripheral vision are tested with the Humphrey or Octopus Automated Field Analyzer in a standardized design (SITA STANDARD 30–2) and analyzed by an ophthalmologist [49]. To measure the ability to detect objects at low contrast, we will measure the contrast sensitivity with the Pelli-Robson charts. This assessment consists of letters arranged in groups with varying contrast, from high to low. Scores are based on the contrast of the last group in which two or three letters were correctly read, this can be calculated in a logarithmic contrast sensitivity score (CSS). In an elderly population (above 60 years old) a CSS lower than 1.50 is considered as decreased contrast sensitivity in [50]. Colour discrimination is the ability to distinguish differences between shades of colours and is divided in primary colours (green, red, blue and yellow) and their axis (red-green, blue-yellow). To evaluate colour vision pseudo-isochromatic plates with coloured dots forming numbers (Ishihara plates) will be used as a screening tool. As a second step the Farnsworth desatured 15D hue test will be performed to evaluate more subtle colour vision deficiencies. This task consists of ordering 15 coloured caps over trays in an incremental manner according to their hue. Colour vision deficiency will be scored in type of colour deficiency and in severity [51, 52].

The examination of ocular motility will be done by an orthoptist. First, we look at eye follow movements, to detect any gaze paresis, nystagmus or saccadic intrusions. Moreover, patients will be asked if they experience diplopia. Diplopia is more common when there is pre-existent ocular misalignment, this is a deviation in the fusion mechanism of the eyes. We use the alternate-cover test at 30 cm and 6 m distance [53] to screen for this. Additionally, convergence insufficiency can cause diplopia and is characterized by an increased near point of convergence (NPC), decreased convergence amplitudes and an exodeviation at near. NPC and exodeviation at near will be measured along a RAF near point rule (Royal Air Force Rule), here we measure if patients can maintain single vision, when trying to focus on an approaching subject. Healthy (young) individuals can avoid double vision until 6 cm in front of their nose. A NPC value that is more than 10 cm from the bridge of the nose is considered abnormal. Convergence amplitudes are measured with a prism, while the patient focuses on a target at near. In general, fusional convergence amplitudes of less than 20 prism diopters at near are a sign of convergence insufficiency [54–56]. In addition, we will use an exploratory Eye-Tracking set up with a Tobii TX300 Eye-Tracker to measure ocular movements and smooth pursuit. Furthermore, we investigate visual and vocal emotion perception and processing using the Emotion Recognition Index (ERI) [57, 58]. This instrument assesses the ability of individuals to correctly infer target emotions from actor portrayals of vocal and facial emotion expressions.

#### Objective assessment

Results of these tests will be obtained without receiving feedback from the patient and are therefore objective measurements. The outcomes are changes in the eyelids, conjunctiva, cornea, fundus, iris and lens opacity, corneal thickness and intraocular pressure, tear production, anatomical changes of the retina including micro vascular changes. First, we examine the eyelids and conjunctiva, followed by inspection of the cornea, iris and using slit lamp examination. This to detect for example blepharitis or conjunctivitis. Lens opacity will be rated with the LOCSIII score, this to evaluate and grade possible cataract [59]. After pupil dilation with tropicamide 0,5% fundus photography is captured. The same experienced ophthalmologist will inspect and grade all fundus images. We will evaluate the macula, retina and vascular structures. This to detect possible presence of macular degeneration, macular edema, vascular pathology, peripapillary atrophy, retinopathy, optic nerve pallor and to evaluate cup-to-disc ratio. A ratio greater than 0.5 may imply glaucoma or other pathology. Furthermore the thickness of the cornea will be measured with pachymetry, this is important because it can mask an accurate reading of the intraocular pressure(IOP). Moreover, a reference range in PD is not known. Pachymetry will be performed after applying local drops of anaesthetics. Corneal thickness ranges between 500 and 575 μm in the healthy population [60]. The IOP will be measured using applanation tonometry (Goldmann tonometer), non-contact tonometry is less reliable [61]. An eye pressure higher than 18mmhg is considered higher than normal and has an increased risk for glaucomatous damage of the optic disc [62]. Complaints of the ocular surface are mainly caused by affections of tear quality and quantity. Tear film quality will be approached by the TearFilmBreakUpTime (TFBUT), while the quantity of tears is will be measured by the Schirmer test. TFBUT is recorded as the time between a complete blink and the appearance of the first randomly distributed dry spot, where a score less than 10 s is considered abnormal [63]. The Schirmer test measures the amount of fluid appearing on the ocular surface within 5 min. For this, paper strips are inserted into the lower fornix with (Schirmer II) and without (Schirmer I) local anaesthesia, and the wet distance is measured in millimetres. Less than 10 mm is considered abnormal and less than 5 is severe [26, 63, 64]. If the Schirmer test and/or TFBUT show lower-than-normal results, the diagnosis “dry eye” or keratoconjunctivitis sicca in case of clinical complaints is made. In Parkinson patients, a reduced eye blink rate EBR may add to an ocular surface disease and dry eye symptoms The EBR is defined as the number of eye blinks per minute measured in a 3-min interval, less than 15 blinks per minute is considered abnormal [26, 65]. Finally, optical coherence tomography (OCT) will be performed to evaluate pattern changes of the retina including the retinal thickness [66–68]. Angio-OCT will be used to inspect the micro vascular changes of the retina [69].

### Statistical analysis plan

95% Confidence intervals, means, standard deviations and frequency distributions will be calculated for all outcomes. Nonparametric variables (age, disease duration, LED, total score VIPD-Q) will be expressed as the median, interquartile range (IQR), minimum, and maximum. To compare groups, we will use the student’s t-test for parametric continuous variables and the Mann-Whitney U test for non-parametric continuous variables. All analyses will be performed with SPSS 22.0 (SPSS Inc., IBM, Chicago, IL, USA).

To address the first study objective (validity of the screening questionnaire), we will compare the results of the VIPD-Q with the ophthalmological assessments using analysis of intraclass correlation coefficient (ICC), with Cohen’s kappa. The results of the ophthalmological assessments will be categorized in visual disorders within the domains of the VIPD-Q (ocular surface, intra- ocular, oculomotor and optic nerve). We hypothesize moderate to good correlation (ICC > 0.5) between the scores on the domains based on the ophthalmological tests and the scores on the domains based on the screening questionnaire. We will also address correlation for the total score. In addition, we will calculate optimal cut-off points of the domains and total score of the VIPD-Q using the receiver operating characteristic (ROC).

For the second and third objective (determine the prevalence and severity of visual problems in PD; impact on clinical functioning), PD patients will be compared with healthy controls using chi-square-tests for categorical values (sex, education, co morbidity, visited ophthalmologist, visual aid, vision changes during the day, difficulties with daily activities, impact on quality of life) or Mann-Whitney U test for non-parametric continuous variables (age, total score VIPD-Q, score per domain). Furthermore, the relationship between falling, disease duration, MDS-UPDRS, hand-eye dexterity, gait and balance tests, and visual problems will be assessed using multiple linear regression analysis.

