## Abstract

**Background:**

Visual disorders are common in Parkinson’s disease (PD) but their exact frequency and severity are unknown. Good visual functioning is crucial for patients with PD, because of their need to compensate for loss of automated motor control and their postural instability, forcing patients to guide their movements visually. Here, we describe the study design of a cross-sectional, multi-centre study aiming to: (1) validate the Visual Impairment screening questionnaire (VIPD-Q, which aims to identify PD patients who should be referred to an ophthalmologist for further assessment); (2) study the prevalence of visual disorders in PD; (3) study the severity and clinical impact of different types of visual disorders in PD; and (4) explore treatment options for ophthalmologic disorders in PD, as a basis for future guideline development.

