## Background

Parkinson’s disease (PD) is the second most common neurodegenerative disease in the developed world. The disease is characterized by a broad range of motor and non-motor symptoms [1]. Non-motor-symptoms include widely recognised examples such as gastrointestinal complaints, cognitive decline or autonomic dysfunction, but also less well appreciated ones such as visual impairment [2]. Visual problems can range from blurred vision, diplopia, reduced colour and contrast vision to visual field deficits, and sore, red, or fatigued eyes. Visual disorders in PD can be caused by different pathological mechanisms like retinal dopamine depletion or decreased dopaminergic innervation of the visual cortex [3, 4].

Almost 80% of visual impairments are treatable or preventable. But to achieve this, timely recognition is obviously pivotal [5]. However, in the field of PD, the presence of visual problems and the resultant visual impairment has remained severely under-recognized, both in research and in clinical practice. This is surprising, since the impact of visual problems is particularly vexing for patients with PD, because of their need to compensate for loss of automated motor control and their postural instability, forcing patients to guide their movements externally (and this include visual guidance) [6]. For example, visual cues such as stripes on the floor are commonly used in clinical practice to overcome freezing of gait [2, 7, 8]. Not being able to see these visual cues adequately may have an immediate impact on functioning in daily life. Indeed, visual disorders combined with postural instability and gait disability can increase the risk of falls and fall-related injuries such as hip fractures and head injuries [9, 10]. Other obvious consequences of visual deficits in PD include problems with driving and reading. Taken together, disorders of vision can lead to reduced physical activity, greater dependence, disability, injuries and reduced quality of life [11–13]. Yet, the exact frequency, type and severity of visual problems are unknown. The few prior studies on this subject showed inconclusive results, in part due to small samples or lack of a complete ophthalmologic examination [14–16]. Since many of these disorders can be treated effectively, educating patients and doctors about them can help to improve quality of life of patients with PD.

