### Phase 1: screening questionnaire

The VIPD-Q was developed by neurologists and ophthalmologists to detect a broad range of ophthalmologic disorders in PD patients. It is based on an extensive literature study, previous questionnaires, and common and disabling visual disorders in both PD patients and healthy older people [2, 11, 13, 15, 17–34]. The questionnaire includes 22 questions on visual problems, plus a standard set of demographic data (Additional file 1: Appendix 1). Answers are given on a 4-point Likert scale ranging from “never have problems” to “daily problems”, without possibility to give a neutral answer. As a second step, we grouped the questions according to the anatomical location of a visual disorder. These domains were agreed upon by a consensus procedure involving three independent ophthalmologists (one from each study site). They were asked to categorize the questions in four domains (Table 1: ocular surface, oculomotor, intra-ocular and optic nerve). Consensus was reached during a meeting with the three ophthalmologists. Six questions could not be categorized in one domain, but rather indicate the involvement of more than one anatomical domain. The VIPD-Q is designed as a patient self-scoring instrument and takes about 20 min to complete.

**Table 1 Tab1:** Domains and corresponding questions with possible diagnosis

Domains	Issues	Possible diagnosis	Question
Ocular surface	lacrimal fluid, eyelids, conjunctiva, cornea	dry eye disease, blepharitis, blepharospasm, conjunctivitis, low eye blink rate,	1: I have blurry vision, when I read or work on a computer. 2: I have a burning sensation or gritty feeling in my eyes. 3: I have mucus/slime or particles in my eyes or eyelids. 4: I have watery eyes.
Intra-ocular	lens, uvea, macula, retina	diabetic retinopathy, macular degeneration, retinal detachment, hypertensive retinopathy, micro-vascular retinopathy, cataract, refraction errors, glaucoma	5: When I read, some letters disappear. 6: Lines that should be straight, appear to be wavy or blurred. 7: I won’t go out alone in the evening or at night because my night vision is insufficient. 8: When I drive at night, the oncoming headlights cause more glare than before.

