### Phase 2: neurological and ophthalmological assessment

#### Patient collective and recruitment

From the responders of phase 1, a sample of 100 patients will be invited for a full clinical and ophthalmological assessment. Patients will be selected based on their scores on the VIPD-Q aiming to include 70 patients with and 30 patients without visual impairment, which is operationally defined as patients scoring the highest 30% or the lowest 30% on the screening questionnaire, respectively. Due to personnel capacity, a sample of 30 patients in the Netherlands (10 in the lowest 30% and 20 in the highest 30%) and 70 patients in Austria (20 in the lowest 30% and 50 in the highest 30%) will be selected and invited for the clinical and ophthalmological assessment. The OLVG hospital only participated in phase 1 of this study. Inclusion and exclusion criteria are described in Table 2. Selection will start after at least 250 questionnaires have been completed. (See Fig. 1).

**Table 2 Tab2:** Inclusion and exclusion criteria

Inclusion criteria	Exclusion criteria
Diagnosis of PD according to the UKPDSBB criteria	Hoehn and Yahr Parkinson’s staging score ≥ 4
The patient must be able and willing to give written informed consent	Secondary cause of parkinsonism as detected by history (e.g. drug-induced parkinsonism)
The patient must be willing to participate in all study related activities and visits	Secondary cause of parkinsonism as detected by investigation (e.g. vascular parkinsonism as detected by neuroimaging)
Age of onset Parkinson’s disease > 30 years	Dementia according to DSM-IV
Stable doses of Parkinson medications ≥4 weeks	Major depressive disorder according to DSM-IV
Current age ≥ 60 years	Psychotic disorder(s) according to DSM-IV
	Prior brain surgery (except deep brain stimulation)
	Previous eye surgery (except phacoemulsification for cataract and artificial lenses)
	Blindness in 1 eye
	Medication that influences normal visual function other than PD medication. (Detailed information, please see Additional file 2: Appendix 2)
	Systemic diseases that may cause eye problems (HIV, DM type I, type II if the patient had ophthalmologic therapy and/or abnormalities at last screening)
	Neurodegenerative diseases other than Parkinson’s disease
	History of lesions near the optic chiasm or occipital cortex
	Migraine

Inclusion and exclusion criteria of the Visual Impairment in Parkinson’s Disease study

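### The promised prevalence and severity of visual disorders in PD cannot be read from unweighted phase 2 frequencies, and the analysis named for that objective gives only self-reported problems

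*Protocol article*

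**What the plan says.** The abstract of the protocol article lists as aims "2) study the prevalence of visual disorders in PD; (3) study the severity and clinical impact of different types of visual disorders in PD". The Background section words the second goal as "determine the prevalence and severity of visual problems in PD", so disorders become problems. The same section calls earlier studies inconclusive, "in part due to small samples or lack of a complete ophthalmologic examination".

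Phase 1 is questionnaire only: at least 750 patients with PD and 250 controls. The VIPD-Q is answered on a 4-point scale running from never to daily problems. Phase 2 is the only part with an eye examination. It has no controls and is "aiming to include 70 patients with and 30 patients without visual impairment", where with and without mean a score in the highest or the lowest 30% of the questionnaire.

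The Statistical analysis plan section opens with "95% Confidence intervals, means, standard deviations and frequency distributions will be calculated for all outcomes". The Subjective and Objective assessment sections call the examination results outcomes, so the sentence covers them. For objectives 2 and 3 the section names comparisons of patients with controls on questionnaire items, total score and domain scores, and a regression of clinical measures and visual problems.

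**The concern.** A disorder found on examination and a problem reported on a questionnaire are different quantities. The article relies on that difference when it faults earlier work for lacking a complete examination, and its Discussion adds that patients may not report eye problems adequately. A reader of the abstract will therefore expect examined prevalence and severity. The only data that could supply them come from a sample built to a quota by VIPD-Q score, with the middle of the distribution left out.

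If phase 2 percentages are published as the frequency of disorders in PD, they will partly reflect the 70:30 quota. A 95% interval around such a percentage covers sampling error but not this distortion. Severity by type of disorder is the most exposed, because the phase 1 scale grades how often a problem occurs, not how severe a disorder is. The article offers this work as a basis for future guidelines, so the difference matters.

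**Working it through.** **Inputs from the protocol article.** Phase 1: 750 patients with PD. Score bands: highest 30%, lowest 30%, and by subtraction a middle 40%. Phase 2: Netherlands 10 low and 20 high; Austria 20 low and 50 high.

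**The plan's own figure.** Low 10 + 20 = 30; high 20 + 50 = 70; total 100. This reproduces the stated sample.

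**Sampling fractions, assuming all 750 are eligible.** The bands hold 0.3 × 750 = 225, 0.4 × 750 = 300 and 0.3 × 750 = 225 patients.
- High: 70/225 = 31.1%
- Middle: 0/300 = 0%
- Low: 30/225 = 13.3%

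High scorers are over-sampled 31.1/13.3 = 2.33-fold against low scorers.

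**Bias of the unweighted frequency.** Let pH, pM and pL be the disorder rates in the three bands.
- Population: 0.3 pH + 0.4 pM + 0.3 pL
- Unweighted phase 2: 0.7 pH + 0.3 pL
- Difference: 0.4 (pH − pM)

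In effect the quota gives the unexamined middle 40% the rate of the high scorers. The documents give no disorder rates, so the following are assumed:

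| pH / pM / pL | Population | Unweighted phase 2 |
|---|---|---|
| 0.4 / 0.4 / 0.4 | 40% | 40% |
| 0.6 / 0.6 / 0.2 | 48% | 48% |
| 0.5 / 0.4 / 0.3 | 40% | 44% |
| 0.6 / 0.4 / 0.2 | 40% | 48% |
| 0.8 / 0.5 / 0.2 | 50% | 62% |
| 0.8 / 0.3 / 0.2 | 42% | 62% |

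The bias runs from 0 to 20 points in these cases.

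**Same question under a model.** Assume that score and liability to a disorder are bivariate normal, with true prevalence 30%. At correlation 0.5, pH is about 0.523 and pL about 0.110, so the unweighted figure is 0.7 × 0.523 + 0.3 × 0.110 = 0.399. Across correlations:

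| Correlation | Unweighted phase 2 (true 30%) |
|---|---|
| 0 | 30% |
| 0.2 | 33.5% |
| 0.3 | 35% |
| 0.5 | 40% |
| 0.7 | 46% |

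**Does weighting the two tails repair it?** Giving the tails equal weight at correlation 0.5 yields (0.523 + 0.110)/2 = 0.316, close to 0.30, but only because the assumed model fills in the middle. Without a model, take pH = 0.6 and pL = 0.2. The tails contribute 0.3 × 0.6 + 0.3 × 0.2 = 0.24 and the middle anything from 0 to 0.40, so prevalence lies between 24% and 64%. If pM lies between pL and pH, the limits are 0.24 + 0.4 × 0.2 = 32% and 0.24 + 0.4 × 0.6 = 48%. The unweighted figure, 48%, is then the upper limit.

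**Precision cost of the tail weights alone.** The weights are 225/70 = 3.21 and 225/30 = 7.5. Kish effective n = 450² / (70 × 3.21² + 30 × 7.5²) = 202,500 / 2,410.7 = 84. Intervals widen by √(100/84) = 1.09, about 9%.

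**The case against.** The strongest reply is that the article never says prevalence will be taken from phase 2. The quoted sentence is generic. The analysis named for objective 2 uses controls, who exist only in phase 1, and the abstract gives the examinations two uses, validating the questionnaire and studying associations. Phase 1 is not enriched by score, and its 95% half-width at n = 750 is about 2.9 to 3.6 points for proportions of 20% to 50%. Its items on daily activities and quality of life also say something about self-reported burden. All of this stands. A reader might infer a stated plan to publish phase 2 percentages as PD prevalence; the text does not support that. What remains is a mismatch: examined prevalence and severity are promised, and either phase 2 supplies them with bias or nothing named does.

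A second reply is that weighting may be left to a fuller analysis plan. That is fair for the weights. It does not cover the middle band, because the design leaves it without observations and any estimate then needs an assumption.

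A reader might also infer from Table 2 that known eye disease has been removed and that diagnoses should be struck from Table 1. That goes too far. Table 2 excludes selected histories, such as "Previous eye surgery (except phacoemulsification for cataract and artificial lenses"), blindness in one eye, and type II diabetes with eye therapy or abnormalities. Cataract, glaucoma, macular degeneration and dry eye are not listed there. Table 1 does include "diabetic retinopathy, macular degeneration, retinal detachment, hypertensive retinopathy", but retinal detachment is not itself an exclusion, and patients with type II diabetes without known eye findings stay eligible. Hemianopsia appears only as a mimic. The exclusions may lower some frequencies; they do not empty a domain.

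**Conclusion.** The point holds in this form: unweighted phase 2 frequencies and their intervals do not estimate the prevalence or severity of examined disorders in PD, and the analysis named for objective 2 yields self-reported problems instead. It does not follow that the study can give no prevalence; phase 1 can give that of self-reported problems.

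The size is conditional. Under the bivariate normal model with true prevalence 30%, the enrichment adds between 0 and about 16 points for correlations from 0 to 0.7. It adds nothing if score and disorder are unrelated, or if the middle band has the same rate as the high band. No correlation of this kind is given in the documents. The sponsor does hypothesise an ICC above 0.5 between questionnaire and examination domains, so a material relation is its own expectation. Because the exclusions may act the other way, a net upward bias should not be asserted for every disorder.

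The sampling fractions and the 9% rest on all 750 responders being eligible. The true values will differ: phase 2 requires age 60 or over and Hoehn and Yahr below 4, one hospital takes part in phase 1 only, and selection starts once 250 questionnaires are in.

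**What to change.** In the Statistical analysis plan section, state that phase 2 disorder frequencies and severity are reported separately for the high and low score strata and are not PD prevalence. Limit objective 2, in the abstract as well, to self-reported visual problems from phase 1 unless the estimate below is given.

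If an overall examined figure is wanted:
- weight each examined patient by the inverse sampling fraction within score band and centre, among responders who meet Table 2;
- predict the middle band from a model of disorder on VIPD-Q score;
- label the result as resting on that interpolation and show bounds for the middle band;
- state that it applies to patients meeting Table 2.

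The minimum change costs only wording and a narrower claim. The overall estimate costs wider, assumption-dependent intervals: about 9% from the tail weights alone if all 750 are eligible, and more once the middle is modelled. Examining a sample of the middle band would remove the interpolation, but it is not a cheap change: the article cites limited personnel capacity and expected phase 2 recruitment to end in May 2019. Table 1 needs no deletions.
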